### The Intervention Group

The patients in the treatment group will be prescribed an individually EBCR program at home and in the hospital. The targeted heart rate and walking distance targets will be set individually based on baseline 6MWT. The intensity progression will be evaluated weekly if tolerated. Exercise education and an exercise guidance book will be provided to patients before the program begins. In the hospital, patients do a 45-minute exercise session consisting of a warm-up (5 min), core exercise (30 min) in the form of walking on a treadmill, and cool down (10 min). This exercise is carried out twice a week over 4 weeks in the hospital (a total of 8 sessions) and is directly supervised by a certified cardiac rehab nurse (Table 1).

During exercise at home, subjects will be monitored by a “TEKAD” telemonitoring system. Patients will wear CovWatch that will be connected via the internet to a web-based system (App Rehab Cardio). Prior to the exercise at home, the researcher and the IT team will ensure that the CovWatch is connected to the dashboard App Rehab Cardio to facilitate the real-time monitoring of patients’ vital signs during exercise (see Figure 2). Home exercise will be carried out for 45 minutes, consisting of 5 minutes of warm-up (eg, simple stretching or slow walking), 30 minutes of core exercise walking based on the exercise dose and patient’s ability, and 10 minutes of cooling down. Vital signs, such as pulse, BP, and oxygen saturation, will be monitored via CovWatch and displayed on the dashboard. Home exercises will be prescribed 3 days a week over 4 weeks (12 sessions in total), with a schedule adjusted by the researchers so as not to coincide with the hospital exercise sessions. Patients will be evaluated and receive weekly exercise reminders directly when they perform exercise at the hospital.

**Figure 2. F2:**
[figure not shown]
Real-time monitoring in home-based exercise cardiac telerehabilitation (HBECTR). CR: cardiac rehabilitation. App Rehab Cardio can be accessed via the web [36].

### Real-Time Monitoring

During exercise at home, subjects will be monitored by a nurse remotely through telemonitoring (TEKAD). With high-precision sensors, the smartwatch “CovWatch” will continuously track the patient’s HR, BP, oxygen saturation level during exercise, and estimated walking distance. The system is connected via the internet to the dashboard (App Rehab Cardio; see Figure 2).

### The Control Group

The CG will be enrolled in a cardiac rehabilitation program in the hospital. Patients in this group also will receive exercise education before starting the program. They will be scheduled for 2 sessions per week or 8 sessions in total to do individual exercise at the hospital under a CR nurse’s supervision. Based on hospital policy, patients are also suggested to exercise at home independently (without monitoring). Hospital exercises consist of a 5-minute warm-up, 30-minute core exercise (walking on a treadmill), and a 10-minute cool-down (Table 1).

### Measurement

In this study, respondents will be asked to fill out the participant characteristics, including age, sex, BMI, and medical history, which were collected at baseline through direct interviews and medical record reviews. Sociodemographic information, such as marital status, educational level, occupation, insurance ownership, and average monthly income, was also gathered. In addition, participants were asked about their smoking history (categorized as current, former, or never smoked) and any past or current illnesses, diseases, or risk factors. Clinical information was obtained, including the patient’s medical diagnosis, ejection fraction, prescribed therapies, weight and height, as well as the schedule of heart polyclinic control and cardiac rehabilitation, if applicable.

Adherence to the exercise-based cardiac rehabilitation program as the primary outcome will be measured by recording the number of sessions attended by each participant. Based on a previous study [40], adherence will be calculated as the number of attended sessions divided by the total number of prescribed sessions, expressed as a percentage, with a minimum of 80% session completion considered adherent. Attendance during in-hospital exercise sessions will be directly monitored by CR nurses and recorded in the CR attendance form, while home-based exercise attendance for IG will be verified through the web-based dashboard system. Adherence will be monitored by smartwatch logs and dashboard analytics. We will apply this comprehensive approach to ensure accurate measurement of each participant’s adherence to the prescribed rehabilitation program.

Functional capacity will be assessed using the 6MWT to measure the total distance (in meters) during 6 minutes test (6-minute walk distance) [19,37]. In addition, physiological data such as HR, BP, and oxygen saturation will be continuously monitored using the telemonitoring system (see Figure 2), ensuring the safety and accuracy of HBECTR. To provide a more comprehensive assessment of functional improvement, peak oxygen uptake (VO_₂_ peak) or metabolic equivalents will be estimated based on the distance covered in the 6MWT, using established predictive equations [41,42]. These measurements collectively will provide robust data on the participants’ functional performance following the intervention.

 The primary and secondary outcomes will be measured after participants have finished the intervention (4-wk follow-up). We selected a 4-week follow-up because this is a pilot feasibility study designed to assess the early feasibility, safety, and adherence of HBECTR. Short-duration assessments are well established and appropriate for pilot and feasibility trials, particularly in digital and cardiac telerehabilitation research [43,44]. Besides, the guideline of CR in Indonesia based on the Indonesia Heart Association also recommends conducting an evaluation after 1 month (4 wk) of phase II CR [19]. Furthermore, early improvements in functional capacity or cardiopulmonary endurance often occur within the first month [5,45], making a 4-week evaluation appropriate for assessing initial signal of effect.

We consider extending the follow-up (3‐6 mo follow-up) for our next trial to ensure the sustainability and efficacy of this program. In addition to feasibility and functional outcomes, we will record hospital readmissions during intervention, and patients will be followed up for 3‐6 months. The ability of patients to do their daily activities will be monitored and recorded using a self-report.

In addition, the implementation outcomes will be assessed using the RE-AIM (Reach, Effectiveness, Adoption, Implementation, and Maintenance) framework [46]. We will report recruitment and representativeness (Reach), adherence and safety (Effectiveness), provider uptake (Adoption), fidelity and dose (Implementation), and short-term intention to continue (Maintenance). Qualitative interviews will be added to explore participants’ experiences and barriers during intervention. Furthermore, we will calculate cost-effectiveness by determining the cost per patient, application development, wearable device production, and internet provision.

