### Study Procedures

To assess the efficacy of the HBECTR program, we divided subjects into 2 groups: the intervention group and the control group (Table 1). The CG will receive standard hospital CR or CBCR, while the treatment group will receive HBECTR. We define HBECTR as exercise-based cardiac rehabilitation conducted in a hybrid setting, both in the hospital and at the patient’s home, supported by a telemonitoring system.

We will use a telemonitoring system consisting of a smartwatch (CovWatch) produced by PT CovWatch Karya Nusantara, Indonesia, connected via the internet to the web-based app (dashboard), namely “Telerehabilitasi Kardiovaskular (TEKAD)” (App Rehab Cardio) [36]. We developed and conducted usability testing before the dashboard was released (will be reported separately). Prior to the initiation of the study, an accuracy test will be conducted on 10‐20 patients as part of the CovWatch protocol. A standardized calibration check will be performed at baseline by comparing CovWatch-derived heart rate (HR) with a clinical pulse oximeter at rest and during walking test. Data validity will be monitored through automated system flags for missing data, connectivity loss, and out-of-range physiological values. Mitigation strategies will include repeating measurements, instructing participants on proper device placement (detailed in the guidance book for patient), verifying battery status, and resynchronizing data in case of delayed transmission. All sensor data will be stored with time stamps to identify anomalies and enable manual quality checks.

Before starting the exercise, all patients will undergo a pretest to measure functional capacity using the 6-minute walk test (6MWT) [37]. This pretest is carried out when the patient is still hospitalized or during the first check-up after PCI, according to hospital policy. The cardiologist will prescribe an exercise regime tailored by patients based on this baseline 6MWT, in accordance with the CR guidelines in Indonesia [19]. After the patients have finished all CR programs, they will do the 6MWT for a posttest. The 6MWT for both pretest and posttest will be done at the CR center, [name] Hospital, Yogyakarta. The intervention of this study will be reported according to the TIDieR (Template for Intervention Description and Replication) [38], in conjunction with the CERT (Consensus on Exercise Reporting Template) [39] and mERA (mHealth Evidence Reporting and Assessment; Checklist1^4^).

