Furthermore, several potential limitations should be acknowledged in this quasi-experimental study. First, the intervention may yield null or minimal effects, particularly on adherence to cardiac rehabilitation and functional capacity, due to variability in participant engagement, baseline fitness levels, or external barriers such as comorbidities or limited motivation. Second, feasibility challenges are anticipated, including variable access to technology, differences in digital literacy, difficulties in remotely monitoring safety, and potential missing data from nonadherence or technical issues. Using a wearable device (smartwatch) is preferable to most patients; however, it has challenges in its implementation and needs further exploration to gain a deeper understanding of patients’ needs and preferences [52]. Finally, resource limitations may constrain implementation, including limited personnel for supervision, insufficient devices for remote monitoring, costs associated with web-based platforms, and the need for staff training and scheduling coordination.

In addition, this study also has limitations, including its modest sample size, and the short follow-up duration limits its generalizability to the broader population. These are intentional features of a pilot feasibility trial that focuses on testing feasibility, safety, and preliminary efficacy signals rather than providing conclusive evidence of effectiveness [32]. Clinical trials of physical activity and rehabilitation interventions are challenging; therefore, researchers can use pilot and feasibility studies to enhance the rigor of future trials [35].

Despite these challenges, the study provides valuable insights into the practicality and potential impact of HBECTR, informing the design of larger, fully powered trials. Future research is needed to enhance the study in multicenters with multiple outcomes. Longer-term effects, sustainability, and cost-effectiveness should be evaluated in a subsequent definitive trial.

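### Home attendance, 60% of the intervention group's prescribed sessions, is known only from the watch and dashboard, and the protocol does not separate a technical failure from a session not done

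*Protocol article*

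**What the plan says.** The Measurement section of the protocol article defines the primary outcome: "adherence will be calculated as the number of attended sessions divided by the total number of prescribed sessions", "with a minimum of 80% session completion considered adherent". It then names the evidence for each setting.

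- Hospital sessions, both groups: "Attendance during in-hospital exercise sessions will be directly monitored by CR nurses and recorded in the CR attendance form".
- Home sessions, intervention group: "home-based exercise attendance for IG will be verified through the web-based dashboard system".
- A further sentence adds: "Adherence will be monitored by smartwatch logs and dashboard analytics".

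The Intervention Group section prescribes 8 hospital and 12 home sessions over 4 weeks. The Control Group section schedules 8 sessions, all at the hospital; home exercise is only suggested there and is not monitored.

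Technical failure is foreseen. Study Procedures states: "Data validity will be monitored through automated system flags for missing data, connectivity loss, and out-of-range physiological values". It adds battery checks, resynchronisation when transmission is delayed, time-stamped storage and manual quality checks. The Discussion lists "potential missing data from nonadherence or technical issues" among the expected challenges. Statistical Analysis Planning intends multiple imputation for missing data without naming the variables it covers.

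**The concern.** The two groups' primary outcome is ascertained by different routes. A nurse sees every control session. Twelve of the 20 intervention sessions are known only through one piece of equipment, since the smartwatch logs and the dashboard both start from the same watch. A flat battery or an unworn or faulty watch leaves the same trace as a patient who did not exercise, namely no data. The Discussion itself places the two causes side by side.

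The protocol describes the validity flags as a check on data quality. It does not connect them to the attendance count, and it names no diary or patient report of home sessions as a second source. If sessions without data enter the numerator as not attended, device reliability is measured as patient behaviour, in one group only. The Introduction says the pilot is meant to examine adherence and digital implementation. A low adherence result would be hard to interpret if the two were mixed.

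**Working it through.** **No figure to reproduce.** The protocol gives no expected adherence and no device failure rate. Its sample size rests on 6-minute walk distance and has no bearing here.

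**Inputs from the protocol.** Intervention group: 8 hospital + 12 home = 20 sessions. Control group: 8 hospital sessions. Cut-off: 80%.

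- Device-dependent share: 12/20 = 60% in the intervention group, 0/8 = 0% in control.
- Cut-off in sessions: 0.80 × 20 = 16 in the intervention group. In control, 0.80 × 8 = 6.4, so 7 of 8.
- One unrecorded home session costs 1/20 = 5 percentage points. A patient who does all 20 sessions falls below the cut-off once 5 are unrecorded (15/20 = 75%).

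**Assumptions, not from the protocol.** Each session is truly attended with probability p, independently of the others. A fraction f of the home sessions actually done leaves no recoverable record and is counted as not attended.

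**Formulas.**

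- Mean recorded adherence, intervention = [8p + 12p(1 − f)]/20, a fall of 0.6·p·f from the true value.
- Share adherent, intervention = P(Bin(8, p) + Bin(12, p(1 − f)) ≥ 16).
- Share adherent, control = P(Bin(8, p) ≥ 7).

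**Worked for p = 0.90.**

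- f = 10%: mean = (7.2 + 9.72)/20 = 84.6%.
- f = 20%: mean = (7.2 + 8.64)/20 = 79.2%.
- Control share = 8 × 0.9⁷ × 0.1 + 0.9⁸ = 0.383 + 0.430 = 81.3%.

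| True attendance p | Home-log loss f | Mean recorded, intervention | Share at ≥16/20, intervention | Share at ≥7/8, control |
|---|---|---|---|---|
| 85% | 0% | 85.0% | 83.0% | 65.7% |
| 85% | 10% | 79.9% | 62.5% | 65.7% |
| 85% | 20% | 74.8% | 40.4% | 65.7% |
| 90% | 0% | 90.0% | 95.7% | 81.3% |
| 90% | 5% | 87.3% | 90.0% | 81.3% |
| 90% | 10% | 84.6% | 81.7% | 81.3% |
| 90% | 20% | 79.2% | 59.5% | 81.3% |
| 95% | 10% | 89.3% | 94.7% | 94.3% |
| 95% | 20% | 83.6% | 78.5% | 94.3% |

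With f = 0 the groups already differ at equal true attendance, because 16 of 20 and 7 of 8 are different hurdles. The comparison with control therefore only gives scale. The effect of log loss is the fall down the intervention column.

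**The case against.** A reader might infer that a home session counts only if it reaches the dashboard, and that every unrecorded session is scored as missed. The protocol states neither rule. It says home attendance is verified through the dashboard, and it also names the smartwatch logs, which may hold a session when only the connection failed. Several provisions work against silent loss:

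- flags, battery checks, resynchronisation, time stamps and manual checks (Study Procedures);
- a connection check before home exercise, and a schedule for home sessions (The Intervention Group);
- remote monitoring by a nurse (Real-Time Monitoring);
- multiple imputation (Statistical Analysis Planning).

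The detailed counting rule may also sit in a fuller document that is not shown. The direction is not certain either, since a watch signal without the prescribed exercise could be counted as attendance.

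Most of this stands, and it rules out the stronger reading. It does not close the gap. Resynchronisation recovers data that were captured late, not data never captured. Manual checks work on stored data, and the remote nurse watches the same feed. Imputation can help only after a session has been identified as missing rather than not done, and the article gives no basis for that distinction. The choice of evidence for the primary outcome is stated in the article, and for home sessions all of it comes from the device.

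**Conclusion.** The point holds as a difference in ascertainment: 60% of intervention sessions depend on the device and no control session does. For a session without recoverable watch data, nothing described tells technical failure from non-attendance. It does not hold as a claim that the plan scores such sessions as missed, or that adherence in the intervention group is certainly understated.

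If they are counted as not attended, mean adherence falls by 0.6·p·f, which is 5.4 points at 90% true attendance and 10% loss. The share reaching 80% falls by 95.7 − 81.7 = 14.0 points at 10% loss and 95.7 − 59.5 = 36.2 points at 20%. With full recovery from the logs there is no effect. All of this rests on assumed attendance, assumed loss rates and independent sessions. A cheap improvement to the derivation is justified; the design need not change.

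**What to change.** The Results section says the intervention ended in both groups in June 2025, so home sessions can no longer be classified as they occur. The stored data can still be used.

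1. Before the analyst is unblinded, match the time-stamped missing-data and connectivity flags and the smartwatch logs to each scheduled home session. Only the intervention group has these sessions, so someone other than the blinded analyst should do this.
2. Put each session in one class: logged; technical failure flagged, attendance unknown; or not done, no flag.
3. Report mean adherence and the share at or above 80% with flagged sessions counted as missed, and again with them counted as attended or removed from the denominator.
4. Report the technical failure rate as a feasibility outcome.

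In the next trial, also record each home session at the hospital visits, where the protocol already has a contact: "Patients will be evaluated and receive weekly exercise reminders directly when they perform exercise at the hospital".

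The cost is some extra derivation work and a range in place of a single adherence figure. A failure that raised no flag would still be classed as not done, so the range does not cover every error.

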### Statistical Analysis Planning

All data will be analyzed using the IBM SPSS software (version 29). We will use MI for missing data. MI is a widely used technique for handling missing data in various fields, including medical, social, and ecological research.

Data analysis will be performed primarily on participants who complete both baseline and postintervention assessments, regardless of their adherence level during the intervention period (*completer analysis*). Participants who withdraw or are lost to follow-up before the posttest will be excluded from outcome analysis but will be included in the descriptive analysis of recruitment, adherence, and retention rates. This approach is considered appropriate for pilot quasi-experimental studies, where the primary aim is to assess feasibility, acceptability, and signal of effect rather than to test definitive efficacy [31,35].

To minimize potential bias due to nonrandom assignment, baseline characteristics between the groups will be compared using 2-tailed independent *t* tests or chi-square tests. In addition, propensity score adjustment will be applied in exploratory models to control for potential confounding variables (eg, age, sex, baseline functional capacity, comorbidity), following recommendations for quasi-experimental design analysis [33].

All statistical analyses and reporting will follow the principles outlined in the CONSORT-EHEALTH 2011 (Consolidated Standards of Reporting Trials of Electronic and Mobile Health Applications and Online Telehealth) [47] (Checklist 3). Descriptive statistics will summarize feasibility outcomes (recruitment, adherence, completion rates, safety events), while inferential tests (2-tailed paired *t* tests or analysis of covariance) will be used to explore within- and between-group changes (including means and SDs) in functional capacity and adherence measures. Statistical significance will be interpreted cautiously, given the pilot nature and limited sample size of the study [31,35].

To analyze the effects of HBECTR on patient adherence as the primary outcome and functional capacity as the secondary outcome, there is no formal multiplicity adjustment planned. The data analysis based on normality assumption will be tested using the Shapiro-Wilk test. If the data comply with the normal assumption, we will use the Student *t* test, and vice versa, nonparametric tests will be used if assumptions are violated. In all statistical tests, *P*<.05 (95% CI) will be considered statistically significant. This structured approach will ensure that statistical methods are properly tailored to the data, supporting robust and meaningful interpretation of the results. The statistical analysis plan has been registered within the protocol to the institutional ethics committee board with the approval number KE/FK/0850/EC/2024.

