**Methods:**

This study is a quasi-experimental nonequivalent control group pretest-posttest. The eligible participants are adults (≥18 y), patients with coronary artery disease after successful PCI, and patients having active health insurance. Patients will be consecutively recruited from [name] Hospital, Yogyakarta, Indonesia, with a minimum of 60 patients after PCI as samples, divided into 2 groups: an intervention group and a comparison or control group. The intervention group will receive hybrid cardiac rehabilitation. Patients will be scheduled to do exercise twice a week at the hospital and 3 times a week at their home. When patients exercise at home, they will have to wear the smartwatch “CovWatch,” which will be connected to the web-based app (App Rehab Cardio) to monitor their vital signs and the distance of walking. The control group will get usual care (center-based cardiac rehabilitation). The data will be analyzed using the Student *t* test to see if the data comply with the normality assumption. This protocol received approval from the institutional review board of the Faculty of Medicine, Public Health, and Nursing UGM (approval number: KE/FK/0850/EC/2024).

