Both groups will be recruited consecutively using identical eligibility criteria, recruitment procedures, and measurement protocols. This study uses a quasi-experimental nonequivalent control group design where the IG was recruited and completed follow-ups before the initiation of the control or comparison group. Sequential, nonconcurrent enrollment was selected due to practical constraints, including a limited number of eligible patients and complete essential preparatory activities and devices (smartwatch and dashboard setup, system testing, and staff training) prior to delivering the hybrid cardiac telerehabilitation intervention. Similar sequential recruitment approaches are common in pragmatic and feasibility trials where randomization or concurrent enrollment is not operationally feasible [26,33].

However, such nonconcurrent enrollment introduces potential time-related biases that statistical adjustment cannot fully eliminate [33]. To mitigate these concerns, we will implement two strategies. First, in the pre-intervention assessment, we will perform demographic and clinical assessments at baseline across both groups. We will carefully select patients based on the eligibility criteria, standardize all outcome measurements (attendance list, 6MWT) using the same instruments and trained team, and apply identical follow-up schedules. These data will help us statistically adjust for any identified differences, although we recognize that such adjustments may not completely eliminate bias. Second, in propensity score matching (PSM), we will plan to use PSM to equate the groups on key variables measured at baseline, which can help balance characteristics across the groups. Baseline demographic and clinical characteristics will be carefully documented, and differences between the groups will be statistically adjusted using multivariable regression and propensity score methods. The use of PSM enabled the construction of a comparison group comprising individuals similar to the treatment group individuals on most observable characteristics [34].

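### Four places give confounder adjustment conflicting roles in a non-randomised comparison, and the only test with a decision rule names no covariate

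*Protocol article*

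**What the plan says.** Four places bear on how the groups will be compared.

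- **Samples** explains that the intervention group finished follow-up before the control group was started. As mitigation it says that "differences between the groups will be statistically adjusted using multivariable regression and propensity score methods" and, for matching, "we will plan to use PSM to equate the groups on key variables measured at baseline". It concedes that adjustment cannot fully remove time-related bias.
- **Statistical Analysis Planning, on non-random assignment**, says baseline characteristics will be compared by t or chi-square tests and that "propensity score adjustment will be applied in exploratory models to control for potential confounding variables". Its examples of confounders are age, sex, baseline functional capacity and comorbidity.
- **Statistical Analysis Planning, on inferential tests**, offers paired t "tests or analysis of covariance) will be used to explore within- and between-group changes" in functional capacity and adherence. No covariates are listed for the ANCOVA.
- **Statistical Analysis Planning, closing paragraph**, opens with "To analyze the effects of HBECTR on patient adherence as the primary outcome and functional capacity as the secondary outcome". It then sets a Shapiro-Wilk check: "If the data comply with the normal assumption, we will use the Student *t* test", otherwise a nonparametric test, with P<.05 as the threshold. The Methods part of the abstract gives only this: "The data will be analyzed using the Student *t* test".

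Baseline 6MWD is measured in all patients before exercise starts (Study Procedures). Age, sex, medical history and ejection fraction are also collected at baseline (Measurement).

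**The concern.** In a randomised trial an unadjusted t test is unbiased and at worst inefficient. Here nothing but eligibility criteria makes the groups alike, so any difference in case mix passes into an unadjusted comparison. Comparing baseline characteristics by significance tests may reveal an imbalance but removes none of it.

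The safeguard that Samples relies on is exploratory in one analysis paragraph and absent from the paragraph that sets the decision rule. An analyst who follows that rule literally reports an effect adjusted for nothing. An analyst who follows Samples reports a regression or a matched comparison. Both could claim to have kept to the protocol, and the Results section says the data are already being analysed.

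This touches both outcomes. Age, sex, comorbidity and baseline capacity can plausibly affect attendance as well as walking distance. The loss of precision from leaving out a baseline value concerns 6MWD only, because adherence has no pretest value.

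**Working it through.** **1. The plan's own figure.** Samples gives a 30 m difference in 6MWD, 80% power, 5% type I error, 10% dropout and 60 patients, but no SD. With n per group = 2(1.960 + 0.842)² × SD² / 30², an SD of 39 m gives 2 × 7.849 × 1521 / 900 = 26.5, so 27. Then 27 / 0.9 = 30 per group and 60 in total. The SD that reproduces 60 is therefore about 39 m (39.3 m is the upper end). At SD 60 m the same formula gives 63 per group, 70 after dropout and 140 in total. Because the SD is not stated, the 60 can be neither confirmed nor refuted. It serves here only to set a range.

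**2. Inputs for the comparison of methods.** From the document: the 30 m difference, two-sided 5%, and 30 per group less 10%, which is 27 completers. Assumptions: SD 39.3, 60 or 80 m; pre-post correlation r = 0.7 or 0.8; a true baseline imbalance B = 20 m. The closing paragraph does not say whether the t test is on the posttest value or on the change, so both are shown.

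**3. Formulas.** The standard error of a difference is s × √(2/27), where s is
- SD for the posttest value,
- SD × √(2(1 − r)) for the change score,
- SD × √(1 − r²) for ANCOVA on baseline.

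Power and rejection rates come from the noncentral t distribution. If posttest = r × baseline + noise with no treatment effect, B shifts the posttest difference by r × B and the change-score difference by −(1 − r) × B.

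**4. Worked case, SD 60 m.**
- Posttest: SE = 60 × 0.272 = 16.3 m, and 30 / 16.3 = 1.84, so power is 44%.
- Change: s = 46.5 m (r 0.7) or 37.9 m (r 0.8), SE = 12.6 or 10.3 m, power 64% or 81%.
- ANCOVA: s = 42.8 or 36.0 m, SE = 11.7 or 9.8 m, power 71% or 85%.
- Leak at B = 20 m: posttest +14 or +16 m, false positives 13% or 16%; change −6 or −4 m, false positives 7.5% or 6.7%.

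**5. Range over SD** (each cell: r = 0.7, then r = 0.8; the posttest power does not depend on r).

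| SD | Power, posttest t | Power, change t | Power, ANCOVA | False positives at B = 20 m, posttest t | Same, change t |
|---|---|---|---|---|---|
| 39.3 m | 79% | 94%, 99% | 97%, over 99% | 25%, 31% | 11%, 9% |
| 60 m | 44% | 64%, 81% | 71%, 85% | 13%, 16% | 7.5%, 6.7% |
| 80 m | 27% | 42%, 57% | 47%, 62% | 10%, 11% | 6%, 6% |

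Under the same model ANCOVA stays at about 5%. A simulation at r = 0.7 and B = 20 m (4,000 runs) gave 5.1% at SD 39.3 m and 5.0% at SD 80 m.

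**6. Limit of the model.** If the groups instead have stable, different mean levels, the change score is unbiased. ANCOVA then under-corrects by (1 − r) × B, which is 4-6 m here, and the posttest comparison carries the full 20 m. In neither case is the unadjusted posttest test the better choice.

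**7. Adherence.** The document gives no expected adherence by group, no spread and no link between covariates and attendance. No size can be computed.

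**The case against.** A fair defence has four parts.

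- **Baseline is in the plan.** A reader might infer that baseline 6MWD is ignored. The document does not support that: ANCOVA is named, baseline functional capacity is among the propensity variables, and a t test on change would use the baseline. Since a paired t test serves within-group change, ANCOVA is the only between-group method in its sentence. One could read the section as ANCOVA for 6MWD and a t or rank test for adherence. That reading is possible, but the closing paragraph applies its test to both outcomes by name.
- **The large losses belong to one reading.** A reader might quote only the drop from 71-85% to 44% power. That needs a posttest-only t test, which no section specifies. Against a change-score t test at SD 60 m, ANCOVA gains about 4 to 7 points.
- **Selective testing.** Taking the smallest P value among t or rank tests (posttest or change) and ANCOVA gives about 11% false positives in simulation. That is not an error rate of this plan: the protocol has a Shapiro-Wilk rule for t versus rank, plans blinded analysts where feasible, and nowhere states such a choice.
- **Pilot status and a separate plan.** The tests are described as exploring a signal, and significance is to be read with caution. Covariate lists and model details may sit in the plan lodged with the ethics committee. This lowers the severity, and a missing list is not the finding. The conflict, however, is in the published text, which also states an aim of evaluating effectiveness and keeps P<.05.

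**Conclusion.** The point holds as an inconsistency that affects the result. Adjustment is a commitment in Samples, exploratory or unranked in part of Statistical Analysis Planning, and absent from the decision rule there and from the abstract. No section names the main estimate, and the rule that carries the significance threshold removes no measured case-mix difference.

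For 6MWD the size is conditional on the assumed SD, correlation and imbalance. It ranges from modest (change-score test, 6-11% false positives at a 20 m imbalance) to serious (posttest test, 10-31%). For adherence, the primary outcome, the bias argument applies but its size is unknown, so a reader should not carry the 6MWD figures over to it. In view of the pilot framing this should be corrected before results are reported, but it does not invalidate the study.

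**What to change.** In Statistical Analysis Planning, name one adjusted main analysis per outcome, with a short covariate list fixed from data already collected.

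- **6MWD:** ANCOVA of posttest 6MWD on group and baseline 6MWD plus, for example, age, sex and comorbidity. Report the adjusted difference with its 95% CI, to be read against 30 m. Give the change score as a sensitivity analysis, since ANCOVA can under-correct in non-randomised groups.
- **Adherence:** a covariate- or propensity-adjusted model of the proportion of prescribed sessions attended.
- **Unadjusted t and nonparametric tests:** supportive only.
- **Abstract and Samples:** align with the above, including whether propensity matching is still intended and in what role.
- **Timing:** because the data are already being analysed, date the change and state whether outcomes by group had been seen.

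The cost is wording and a rerun of the models; no new data are needed. The adjusted estimate may be less favourable than the raw difference. Adjustment will not remove the calendar-time bias from sequential enrolment, and the report should repeat the concession that Samples already makes.
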